**Fig 9 pone.0310178.g009:**
[figure not shown]
Pittsburgh Rehabilitation Participation Scale and newly defined exercise sessions.

The secondary outcome measures are the number and percentage of participating sessions, the number and percentage of effortful sessions, the number and percentage of successful sessions, the mean amplitude of muscle contractions in a session, and the duration and percentage of participating sessions during self-exercises. Rivermead Motor Assessment, Manual Muscle Test for muscle strength, BRS, Fugl–Meyer Assessment of the Lower Extremities, Berg Balance Scale, Functional Ambulation Category, modified Rankin scale, and Short-Form Health Survey version 2. As a muscle strength measurement test, the Manual Muscle Test is evaluated on a scale of 0–5 according to strength against gravity and resistance. In this study, the Manual Muscle Test of the hip flexor, hip abductor, knee extensor, and ankle dorsiflexor will be measured. Manual Muscle Test has good external and internal efficacy and is not dependent on examiner bias [31]. The BRS is a classification method that models the motor recovery process after stroke-induced hemiplegia on a 6-point ordinal scale. The Brunnstrom approach focuses on the unique patterns associated with stroke recovery, including spasticity development, synergistic patterns, and voluntary movements. The BRS has high inter-rater reliability (0.74–0.98) [32]. The Fugl–Meyer Assessment of the Lower Extremities investigates hip, knee, and ankle movements, and hierarchical recovery is recorded based on Brunnstrom stages of recovery from reflex to synergistic and non-synergistic movements. The Fugl–Meyer Assessment of the Lower Extremities motor domain uses a 3-point ordinal scale: 0, unable to perform; 1, partial performance; and 2, complete performance. Possible scores range from 0 to 34. The intra- and inter-rater reliabilities are excellent in early stroke patients [33]. The Berg Balance Scale was developed to objectively measure balance and fall risk in community-dwelling older adults using a three-step survey of 32 health professionals. The Berg Balance Scale examines 14 movements of daily life on a 5-point ordinal scale from 0–4, and the total score ranges from 0–56. The Berg Balance Scale is widely used to assess stroke patients, and its test-retest reliability and internal consistency are excellent [34]. The Functional Ambulation Category is a 6-point rating scale that assesses the amount of human support required when walking (with or without a personal assistive device). A score of 0 indicates a non-functional ambulator, and a score of 1–3 indicates a dependent ambulator. A score of 1 indicates the need for continuous manual contact, 2 indicate intermittent or continuous light touch, and 3 indicates supervision or verbal cues. Scores of 4–5 indicate an independent ambulator, with a score of 4 indicating independent ambulators on horizontal surfaces only and a score of 5 indicating independent ambulators on any surface, including stairs. There is good inter-rater reliability among examiners in post-stroke patients [35]. The modified Rankin scale is a widely used tool to measure global disability after stroke. The scale classifies disability from 0 (no symptoms) to 5 (severe disability). Scoring is performed by an evaluator based on patients’ functional dependence. The intra-rater reliability is excellent [36]. The Rivermead Motor Assessment consists of three sections, and sections of gross function and leg and trunk are evaluated in this study. The gross function section consists of 13 items and primarily assesses mobility from sitting to running and gait, and the leg and trunk section describes individual movements of the trunk (e.g., rolling to the affected side) and leg (e.g., ankle dorsiflexion with the leg extended while lying down). The intra-class correlation coefficients of the Rivermead Motor Assessment is between 0.88 and 0.95 [37]. The Short-Form Health Survey version 2 is a well-studied self-reported measure of functional health. The items include physical functioning, physical role limitation, pain, general medical health, vitality, social functioning, emotional role limitation, mental health, physical component scale, and mental component scale. There is good internal consistency of >0.7 for all the subscales of the questionnaire [38]. Among the assessments for the baseline status and primary and secondary outcomes, the official Korean version of the Fugl–Meyer Assessment, Berg Balance Scale, Short-Form Health Survey 36 version 2, and the Hospital Anxiety and Depression Scale will be used in this study [39–42]. The assessors who are proficient in English will conduct the English version of the assessments, including the Pittsburgh Rehabilitation Participation Scale, Rivermead Motor Assessment, Manual muscle test, Brunnstrom recovery stage, modified Rankin scale, and Functional Ambulation Category. The Short-Form Healthy Surgery 36 version 2 and the Hospital Anxiety and Depression Scale are self-administered questionnaires, and all other evaluations are clinician-administered assessments. All primary and secondary outcomes will be assessed at baseline, and at 3 weeks and 12 weeks. Assessments will be performed over two days to manage fatigue and reduce potential bias in stroke patients. The Fugl–Meyer Assessment, Berg Balance Scale, Manual muscle test, and Short-Form Health Survey 36 version 2 will be conducted on the first day, and the Rivermead Motor Assessment, Brunnstrom Recovery Stage, modified Rankin Scale, and Functional Ambulation Category will be conducted on the second day. Participants will be instructed and familiarized before the actual assessments to help them understand the evaluation processes and improve compliance. Regular breaks will be provided during assessment sessions to prevent fatigue and maintain the participants’ attention.

The schedule of enrollment and assessment of the patients is shown in Fig 10. After admission, patients will be screened according to the inclusion criteria. After screening, the guardians of patients who met the inclusion criteria will be given an information sheet and asked to provide written consent to participate in the trial. Patients are then enrolled in the trial, given a trial-specific identification number, and randomly allocated to a group using a computer-generated random sequence listed prior to the start of the trial. After baseline evaluation, patients will be assessed at 3 and 12 weeks. The intervention period consists of 3 weeks of in-bed self-exercises based on EMG sensor feedback. Assessments at 12 weeks serve as a follow-up evaluation for the long-term effects after a 3-week intervention.

**Fig 10 pone.0310178.g010:**
[figure not shown]
Schedule of enrollment and study assessments. PT, Physical therapy; EMG, Electromyography; PRPS, Pittsburgh Rehabilitation Participation Scale; RMA, Rivermead Motor Assessment; MMT, Manual Muscle Test; BRS, Brunnstrom Recovery Stage; mRS, Modified Rankin Scale; FMA-LE, Fugl–Meyer Assessment of the Lower Extremities; FAC, Functional Ambulation Category; BBS, Berg Balance Scale; SF-36v2 36-item Short-Form Health Survey version 2.

### 2.6. Adverse events

Potential adverse events, including falls, fractures, severe pain, symptoms of respiratory or hemodynamic instability (e.g., dyspnea, tachypnea, dizziness, arrhythmia, bradycardia, high or low systolic blood pressure, or oxygen desaturation), and discomfort at the sensor attachment sites, will be monitored during exercises. To prevent falls, in-bed self-exercises should be performed with the bed rails raised, which are instructed to participants and their caregivers. If an adverse event occurs, the principal investigator promptly reports and documents it to the IRB.

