# Protocol for a single-blind randomized controlled clinical trial to investigate the feasibility and safety of in-bed self-exercises based on electromyography sensor feedback in patients with subacute stroke

**DOI:** 10.1371/journal.pone.0310178

**Published:** 2024-12-30

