## Abstract

**Background:**

The dosage and intensity of physical therapy are crucial factors influencing the motor recovery of the hemiplegic lower limb in patients with subacute stroke. Biofeedback using wearable sensors may provide opportunities for patients with stroke to effectively guide self-exercises with monitoring of muscular activities in hemiplegic lower limbs. This study aims to explore the feasibility and safety of in-bed self-exercises based on electromyography sensor feedback in patients with subacute stroke.

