The primary outcome measure is the Pittsburgh Rehabilitation Participation Scale (PRPS). The PRPS is a clinician-administered instrument designed to assess the participation of patients in rehabilitation [29, 30]. It is rated on a scale of 1–6 to measure a patient’s effort and activity to participate in rehabilitation. The patient’s session participation and effort levels were assessed across six distinct categories, ranging from "none" to "excellent." The "none" category signifies that the patient either declined to participate in the entire session or did not engage in any exercises during the session. Conversely, the "excellent" category denotes that the patient actively participated in all exercises with maximal effort, successfully completing each exercise and displaying a keen interest in both the exercises and any future therapy sessions. The remaining categories describe varying degrees of participation and effort between these two extremes [30]. In the PRPS, there are three types of exercise sessions to be newly defined as follows: (i) a participating session, in which the number of contractions of target muscles is more than one; (ii) an effortful session, in which the amplitude of one or more target muscles during contractions is more than 20% of maximal voluntary isometric contraction; (iii) a successful session, a session in which the amplitude of one or more target muscles during contractions is more than 50% of maximal voluntary isometric contraction. The six categories of PRPS using the concept of participating, effortful, and successful sessions are defined as follows: (i) none, 0% of participating sessions; (ii) poor, <50% of participating sessions; (iii) fair, ≥50% of participating sessions and <50% of effortful sessions; (iv) good, ≥90% of participating sessions, ≥50% and <90% of effortful sessions; (v) very good, ≥90% of participating sessions, ≥90% of effortful sessions, and ≥90% of successful sessions; (vi) excellent, ≥90% of participating sessions, ≥90% of effortful sessions, ≥90% of successful sessions, and active involvement in establishing exercise plans for future sessions (Fig 9).

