### 2.8. Statistical methods

All statistical analyses will be performed for intention-to-treat and a per-protocol population. Descriptive statistics, including mean and standard deviation, median and range, or number and percentage, will be provided for all assessed outcomes. To investigate the effects of time and groups on outcome variables, a repeated measures design with a linear mixed model will be employed. The linear mixed model will include time (baseline, 3 weeks, and 12 weeks), group (control and intervention groups), and time*group interaction as fixed effects, while sex, height, and weight will be treated as random effects. Assumptions of normality, independence, and homoscedasticity will be checked to ensure the validity of the model. Effect sizes with 95% confidence intervals will be calculated. Missing data will be handled using multiple imputation or maximum likelihood estimation. A two-tailed approach will be used. The significance level will be set at p<0.05. All statistical analyses will be conducted using SPSS (version 25.0; IBM, Armonk, NY).

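### Safety is an aim in the title, but adverse events are in no outcome list and the one monitoring window written is exercise time, which differs between arms by design

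*Protocol article*

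**What the plan says.** The title presents a trial to "investigate the feasibility and safety of in-bed self-exercises based on electromyography sensor feedback in patients with subacute stroke". The abstract repeats the aim ("This study aims to explore the feasibility and safety of in-bed self-exercises"), and its conclusion says that the trial will estimate both.

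Section 2.5.1 names the Pittsburgh Rehabilitation Participation Scale as the primary outcome. The secondary list opens with "The secondary outcome measures are the number and percentage of participating sessions, the number and percentage of effortful sessions" and goes on to EMG amplitude, session duration, motor, balance, walking and disability scales, and a quality-of-life questionnaire. No adverse event measure appears there, in the abstract's list, or in the captions of Figs 2 and 10 (the figures themselves are not shown).

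Section 2.6 lists falls, fractures, severe pain, breathing or circulatory symptoms and sensor-site problems, and closes the list with the window: "discomfort at the sensor attachment sites, will be monitored during exercises". It gives no other window and no collection at the week 3 or week 12 visits. It then adds a reporting rule: "If an adverse event occurs, the principal investigator promptly reports and documents it to the IRB".

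Section 2.8 plans descriptive statistics that "will be provided for all assessed outcomes", and intention-to-treat and per-protocol analyses. Section 2.7 says that a participant whose discomfort persists leaves the study and that the data already collected are left out of the analysis.

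**The concern.** One of the two stated aims has no outcome attached, and the single rule on looking for harms ties the search to exercise sessions. The arms are prescribed different amounts of exercise, so they are watched for different lengths of time. Two things are at stake.

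- **Completeness.** Events in the rest of the day, or those that appear after a session ends, are not actively looked for in either arm.
- **Comparability.** A background event that both arms suffer equally has more chance of being recorded in the arm with more sessions.

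The choice of outcomes and the observation window is protocol content. No analysis plan can later recover events that nobody asked about.

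**Working it through.** The article states no exposure time and no expected event rate, so there is no safety figure to reproduce. Its one related figure, the sample size in section 2.1, does reproduce: 20 / (1 − 0.15) = 23.5, rounded up to 24, or 12 per group.

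**Inputs**
- Conventional therapy, both arms (section 2.4.1): 30 min × 2 per day × 5 days = 300 min per week.
- Self-exercise, intervention arm only (section 2.4.2): at least 30 min × 2 per day × 5 days, for 3 weeks.
- Recommended range of self-exercise (section 2.4.2, principle F): 2 to 3 sessions per day. That a third session also lasts 30 minutes is my assumption.

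**Prescribed exercise time over 3 weeks**
- Control: 300 × 3 = 900 min.
- Intervention, two sessions a day: 900 + 30 × 2 × 5 × 3 = 900 + 900 = 1,800 min; ratio 1,800 / 900 = 2.0.
- Intervention, three sessions a day: 900 + 30 × 3 × 5 × 3 = 900 + 1,350 = 2,250 min; ratio 2.5.

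**How far the ratio moves under other assumptions**
- Incomplete adherence to two self-exercise sessions a day, with conventional therapy fully attended; ratio = (900 + a × 900) / 900. At assumed a = 50%, 75% and 90% this gives 1.5, 1.75 and 1.9.
- Conventional therapy continued and monitored to week 12 (not stated): control 300 × 12 = 3,600 min; intervention 3,600 + 900 = 4,500 min; ratio 1.25.
- The word exercises in section 2.6 read as the in-bed programme only: control time is 0 and no comparison exists. The next sentence there, on bed rails during in-bed self-exercise, makes this reading possible.
- Same calendar window in both arms: ratio 1.0.

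**Share of the 3 weeks inside the window**
- Calendar time: 3 × 7 × 24 × 60 = 30,240 min.
- Control: 900 / 30,240 = 3.0%.
- Intervention: 1,800 / 30,240 = 6.0%.

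In both arms about 94% or more of the 3 weeks therefore lies outside the written window, at two self-exercise sessions a day.

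**Sections 2.7 and 2.8 side by side.** Section 2.6 counts sensor-site discomfort as an adverse event. Section 2.7 removes the data of anyone excluded because discomfort persists, without saying which kind. Section 2.8 promises an intention-to-treat analysis. A patient who could not tolerate the sensor could thus vanish from the safety data, and the two sections conflict.

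**The case against.** The strongest reply is that the aim concerns the safety of in-bed self-exercises, so watching patients while they do them is a relevant window. The article's hypothesis compares the arms on participation only, and no between-arm safety test is announced. That stands in part: session-related events deserve their own display. But delayed pain and skin reactions after sensor removal also bear on the safety of the intervention, and in a randomised trial the control arm is what separates background events from those due to the intervention.

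Several stronger readings are tempting, and the document does not support them.

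- *Events outside sessions are missed.* Section 2.6 does not say that monitoring is limited to sessions, and its ethics-board sentence is not tied to them, so a ward fall may well be reported. What is absent is a planned and equal search.
- *Adverse events will never be reported by arm.* Section 2.8 does not name them, but tabulation is commonly left to an analysis plan, which is not shown.
- *The intervention arm is actually watched at least twice as long.* The factor of 2 is prescribed time over 3 weeks; imperfect adherence or longer monitoring of conventional therapy lowers it.
- *The intervention arm would show 2.0 to 2.5 times the events.* This assumes a hazard per minute of exercise. Extra events in added sessions would then be a real effect of the intervention, which a safety evaluation should capture. Observation bias applies to background events that controls also have but nobody seeks, and the document gives no rate from which to size it.
- *The arms differ in self-report against therapist observation.* Section 2.6 does not say who monitors, or how.
- *With no events, the upper limit is large.* The exact two-sided 95% limits are 1 − 0.025^(1/12) = 26.5% for 0 of 12 and 1 − 0.025^(1/10) = 30.8% for 0 of 10. They reflect a pilot of this size and would be the same under any window.

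**Conclusion.** The point holds in a limited form. Safety is an aim, no outcome list contains adverse events, and the one written window is exercise time. Over the 3 weeks that window is prescribed as 900 against 1,800 minutes, or 2,250 with three 30-minute sessions a day. The actual ratio depends on adherence, on how long conventional therapy is monitored, and on what the word exercises covers. Background and delayed events are not systematically sought outside sessions, and any between-arm comparison carries a difference in observation time whose effect on event counts cannot be sized from the document. Removing the data of patients excluded for persistent discomfort adds a further gap and contradicts the intention-to-treat analysis. This calls for an inexpensive improvement; it does not show that the trial will fail to detect harm.

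**What to change.** - In section 2.5.1, name adverse events as a safety outcome.
- In section 2.6, replace the session-bound window with a calendar window common to both arms: randomisation to week 3, and again at week 12. Use the same questions, whether or not the patient was exercising, at contacts that already exist in both arms.
- Flag events that occur during self-exercise and show them separately, with exercise time as denominator.
- Report the number of patients with at least one event per arm, with exact 95% confidence intervals, for all randomised patients.
- Reconcile section 2.7 with section 2.8, so that safety data from patients excluded for persistent discomfort stay in the analysis.

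The cost is a little more data entry and one table. A sensor-site question would reveal the allocation, so staff who are not blinded should ask it. Nothing in the treatment of either arm changes.

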### 2.7. Management

The researchers will ensure the protection of participant anonymity and the confidentiality of data related to individuals, safeguarding their identities and any identifying information. Clinical records, research instruments, or any documents containing participant data will be identified by a code instead of the participant’s name, even when submitted to regulatory institutions or sponsors. The researchers will secure the records of the participants and maintain the confidentiality of information regarding codes, names, and addresses, limiting access to only the researchers. All files will be stored in a dedicated, secure location within a single folder for this study.

Participation in this study is entirely voluntary, and non-participation will not impact the patient’s medical follow-up or the relationship between the team and the patient. Upon signing the consent form, patients may choose to withdraw from the study at any time without consequences regarding their treatment or follow-up at the institution.

The risks during the research are expected to be minimal. The evaluation may be temporarily halted to allow for necessary medical interventions. However, if discomfort persists, the participant will be excluded from the research, any collected data will be excluded from analysis, and the patient will not be reassigned to another group.

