Self-exercises under intermittent supervision by physical therapists could serve as an alternative to efficiently augment the training volume for hospitalized stroke patients [16, 17]. Self-exercises are a crucial component of strategies such as telerehabilitation and self-administration to increase the dose of rehabilitation training [18, 19]. A recent systematic review showed that the effect of self-exercises on post-stroke motor function was equivalent to that of conventional rehabilitation [20]. However, although self-exercises can help compensate for the shortage of training during hospitalization [21, 22], its inherent limitations, such as its repetitive nature and lack of feedback, may restrict its effectiveness in improving motor recovery [23, 24].

Wearable electromyography (EMG) sensors can be utilized to acquire data on muscular activity, potentially enabling monitoring of the quantity and quality of self-exercises and tailoring rehabilitation programs for individual patients by adjusting the grades of self-exercises. This study aims to investigate the feasibility and safety of in-bed self-exercises based on EMG sensor feedback in patients with subacute stroke. Towards this goal, we developed a novel self-exercise protocol incorporating wearable EMG sensors to provide biofeedback to stroke patients. In this study, we hypothesize that there will be a statistically significant difference in Pittsburgh Rehabilitation Participation Scales among subacute stroke patients who receive conventional lower extremity rehabilitation compared to those who receive rehabilitation based on feedback using data obtained via electromyography-supervised self-exercise. Specifically, the null hypothesis (H₀) posits no significant difference between the two groups, while the alternative hypothesis (H₁) posits a significant difference in the participation scales.

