### 2.2. Eligibility criteria

The inclusion criteria are as follows: (1) age ≥19 years [6]; (2) the onset of stroke ≤3 months [6]; (3) muscle strength at the paretic lower limbs, grade ≤4 as per the Medical Research Council grading scale; (4) modified Rankin Scale 2–5 points; and (5) cognitively able to understand and follow instructions. The exclusion criteria consist of (1) recurrent stroke resulting in neurological deterioration during the study period; (2) other neurological abnormalities that affect balance or gait function (e.g., Parkinson’s disease); (3) severe cognitive impairment; (4) serious or complex medical conditions (e.g., active cancer); and (5) implanted electrical stimulators, which can interfere with measurements of EMG activity (e.g., pacemaker, deep brain stimulator).

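### Discarding the collected data of allocated participants whose discomfort persists contradicts the intention-to-treat analysis and takes a listed type of adverse event out of the analysed results

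*Protocol article*

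**What the plan says.** The protocol article, section 2.7 (Management), allows an evaluation to be paused for medical reasons and then states: "if discomfort persists, the participant will be excluded from the research, any collected data will be excluded from analysis". The sentence ends by saying that "the patient will not be reassigned to another group", so it concerns people who already belong to a group.

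Section 2.8 (Statistical methods) states: "All statistical analyses will be performed for intention-to-treat and a per-protocol population". It adds: "Missing data will be handled using multiple imputation or maximum likelihood estimation". Neither section exempts the intention-to-treat set or the safety results from the rule in 2.7.

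Section 1 gives the aim: "This study aims to investigate the feasibility and safety of in-bed self-exercises based on EMG sensor feedback in patients with subacute stroke". Section 2.6 lists the potential adverse events. Severe pain is among them, and the list ends with "discomfort at the sensor attachment sites, will be monitored during exercises". The same section says: "If an adverse event occurs, the principal investigator promptly reports and documents it to the IRB".

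A related wording point is in section 2.2, where the first exclusion criterion is "recurrent stroke resulting in neurological deterioration during the study period".

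**The concern.** Intention-to-treat keeps every randomised participant in the arm assigned, whatever happens afterwards. The rule in 2.7 removes a participant, and everything already measured on that participant, because of something that happens after allocation. If the rule is followed, the set called intention-to-treat consists of randomised participants without persistent discomfort.

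In most trials this would be a moderate problem. Here tolerability is part of the question. Participants with persistent discomfort are among those from whom a feasibility and safety trial learns most, and the rule takes them out of its results. With 12 participants per arm, each removal is 1/12 = 8.3% of an arm.

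The primary outcome, the Pittsburgh Rehabilitation Participation Scale (PRPS), could also be affected. It measures participation and effort, and someone in continuing discomfort may well participate less. If such participants are dropped, the mean of those who remain rises.

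**Working it through.** **1. The passages side by side.**

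- Section 2.7: the trigger is persistent discomfort; the participant is already allocated; all collected data leave the analysis.
- Section 2.8: all analyses are run on an intention-to-treat population, as well as a per-protocol one.
- No sentence limits the 2.7 rule to the per-protocol set or exempts the safety results.

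The two statements therefore conflict as written.

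**2. Can the missing-data methods rescue it?** Maximum likelihood and multiple imputation draw on what was observed for a participant, such as the baseline value or a 3-week value, to account for what was not. The rule discards those observed values. A participant with no data contributes nothing to the likelihood and gives imputation nothing individual to work from.

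**3. The plan's own figure.** Section 2.1 takes 20 participants and a 15% loss: 20/(1 − 0.15) = 23.5, rounded up to 24, or 12 per group. This reproduces. Four removals would leave 24 − 4 = 20, so the allowance protects the number of participants. It does not protect against selective removal.

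**4. Effect on the analysed rate of persistent discomfort.** The documents give no discomfort rate, so the number affected, k of 12 in one arm, is an assumption, shown from 1 to 4. Data kept: rate = k/12. Rule applied: rate = 0/(12 − k). The intervals are exact (Clopper-Pearson) 95%.

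| k (assumed) | Data kept | Rule applied |
|---|---|---|
| 1 | 1/12 = 8.3% (0.2 to 38.5%) | 0/11 = 0% (0 to 28.5%) |
| 2 | 2/12 = 16.7% (2.1 to 48.4%) | 0/10 = 0% (0 to 30.8%) |
| 3 | 3/12 = 25.0% (5.5 to 57.2%) | 0/9 = 0% (0 to 33.6%) |
| 4 | 4/12 = 33.3% (9.9 to 65.1%) | 0/8 = 0% (0 to 36.9%) |

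The right-hand rate is zero by construction, whatever k is.

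**5. Possible effect on PRPS.** Suppose k of 12 participants score L and the others score H. Mean with all kept = (kL + (12 − k)H)/12. Mean after removal = H. Shift = k(H − L)/12. With k = 2, L = 2 and H = 5, the mean goes from (4 + 50)/12 = 4.50 to 5.00. Over k = 1 to 3, L = 1 to 3 and H = 4 or 5, the shift runs from 1 × (4 − 3)/12 = 0.08 to 3 × (5 − 1)/12 = 1.00 points on the 1 to 6 scale. All these values are assumed, and taking L below H builds in the upward direction. They show how the mechanism works, not its expected size.

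**The case against.** The strongest reply concerns scope. The sentence in 2.7 follows one about halting an evaluation, so it may have been meant for discomfort during outcome assessments, which both arms undergo. It does not mention sensors. That reading is fair, and it weakens any claim about one arm. It does not remove the contradiction: the sentence is not limited to assessments, and even on the narrow reading it drops the data of randomised participants.

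Four stronger readings are tempting, and the documents do not support them.

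- **That randomisation is broken in one arm and the results favour the device.** The sensors belong to the self-exercise intervention, so greater loss in that arm is possible. It is not shown, and nothing in the documents ties discomfort to low PRPS scores. Section 2.7 also expects risks to be minimal.
- **That the adverse events disappear.** Section 2.6 requires them to be documented and reported to the IRB. They leave the analysed results, not the record.
- **That data are deleted after recurrent stroke.** Section 2.2 does not say so. Its fault is smaller: an exclusion criterion that depends on an event during the study cannot be assessed at screening.
- **That the per-protocol analysis selects on the primary outcome.** This would follow only if the per-protocol set were defined by adherence to self-exercise. The article gives no definition, and a statistical analysis plan that is not shown may supply one. No point is made of it here.

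**Conclusion.** The contradiction between sections 2.7 and 2.8 stands on the text alone and needs no numerical assumption. The certain consequence of applying the rule is that the analysed rate of persistent discomfort is 0% whatever its true value, so a stated aim of the trial could not be met for that event. How much would be hidden depends on a rate that the documents do not give. The direction and size of any bias in PRPS cannot be estimated from them either; an upward shift in the intervention arm is a possibility only.

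This should be corrected before analysis. The recurrent-stroke criterion is a minor wording point alongside it.

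**What to change.** Reconcile sections 2.6, 2.7 and 2.8 by separating the end of participation from the use of data:

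- In 2.7, remove the clause that excludes collected data from analysis.
- State instead that, subject to consent, data collected up to discontinuation are kept, and that the participant is analysed in the randomised arm under intention-to-treat with the missing-data methods of 2.8.
- State that the event is counted in the safety and feasibility results as well as reported to the IRB.
- In 2.2, reconcile the recurrent-stroke criterion with the intention-to-treat statement by recording such a stroke as an on-study event with data retained.

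When exercise or assessment should stop remains a clinical decision, and none of these changes touches it. The cost is a few sentences of protocol wording. The sample size stays at 24, and the intention-to-treat denominator stays at 12 per arm.
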